# Group-based exercice training programs for military members presenting musculoskeletal disorders – protocol for a pragmatic randomized controlled trial

**DOI:** 10.1186/s12891-022-05317-6

**Published:** 2022-04-18

**Keywords:** Musculoskeletal disorders, Low back pain, Rotator cuff related pain, Ankle sprains, Patelofemoral pain syndrome, Physiotherapy, Group-based intervention, Individual intervention, Randomized controlled trial

## Abstract

**Background:**

Musculoskeletal disorders are a leading cause of morbidity and the most prevalent source of disability among soldiers. Their high prevalence in armed forces and limited ressources have led to problems related to access to physical rehabilitation care. To increase access, supervised group-based exercise programs for the most prevalent musculoskeletal disorders (low back pain, patellofemoral pain, rotator cuff-related shoulder pain or lateral ankle sprain) have been developed at a Canadian Armed forces (CAF) base, but their effectiveness has not been evaluated. The primary objective of this randomized controlled trial is to evaluate the mid- and long-term effects of these group-based training programs on pain severity and functional limitations, in comparison with usual individual physiotherapy care. Secondary objectives include comparing both interventions in terms of health-related quality of life, pain-related fear, and patients’ satisfaction.

**Methods:**

One hundred and twenty soldiers with a new medical referral for physiotherapy services for one of the four targeted musculoskeletal disorders will be consecutively recruited. They will be randomly assigned to either group-based training program or usual individual physiotherapy care, and will take part in the assigned 12-week intervention. There will be four evaluation sessions over 26 weeks (baseline, week 6, 12 and 26). At each follow-up, functional limitations, pain severity, health-related quality of life and pain-related fears will be assessed. Patients satisfaction with treatment will also be evaluated at the end of the intervention period. Either two-way repeated measures ANOVA will be used to analyse and compare the effects of the interventions.

**Discussion:**

This RCT will determine the effectiveness of group-based training programs compared to usual individual physiotherapy care. This new intervention model could represent an efficient, and more pro-active approach to manage a higher number of soldiers with musculoskeletal disorders. It could improve access to physical rehabilitation care and improve the health of soldiers.

**Trial registration:**

ClinicalTrials.gov (NCT05235152), February 11th 2022.

## Background

Musculoskeletal disorders (MSKd) affect 20 to 33% of the world’s population [1, 2]. Due to their great prevalence and their important consequences on physical and mental health [3], MSKd are the leading cause of loss of productivity and invalidity worldwide [2]. Conservative management, including rehabilitation interventions such as education and exercises, is well recognized as a first choice therapeutic option for persons presenting these disorders [4]. However, limited access to such outpatient physical rehabilitation services has been identified as a major problem in many countries [5–8]. Access to these services is notably limited by long wait times, leading to increased disability and invalidity [3, 9].

Members of Armed Forces are among those affected by extensive waiting times to access physical rehabilitation services [10]. MSKd are a leading cause of morbidity and the most prevalent source of disability among military personnel [11–13]. They also represent the main medical cause of restricted duties and days off work, and the main reason for not being able to deploy [13, 14]. In the last decade, the increased operational tempo, the aging of soldiers, and the changing nature of the missions have led to a higher number of non-battle-related MSKd [14, 15]. The management of MSKd in a timely manner has thus become a huge challenge.

Physical rehabilitation among military members with MSKd requires innovative effective interventions to optimize the use of ressources and increase access to these services. As the literature encourages the use of active exercises for the management of MSKd [4, 16], the development of a tailored supervised group-based exercise approach could represent an option of choice. Supervised group-based exercise programs have been shown to reduce wait times to rehabilitation services [17] and to be effective in the management of MSKd [18]. However, the majority of studies until now have evaluated group-based interventions for chronic low back pain [18]. In the last 10 years, three supervised group-based exercise programs supervised by physiotherapists (PT) and physiotherapy technologists (Phys. T.) have been developed at one of the Canadian Armed forces (CAF) bases (Valcartier) (Lumbar Training Program for for low back pain; Upper Extremity Training Program for rotator cuff-related shoulder pain; Lower Extremity Training Program for patellofemoral pain syndrome and lateral ankle sprain). They were developped to increase access to physical rehabilitation care regarding the most prevalent MSKd, as CAF statistics show the lumbar spine, knee, ankle and shoulder are by far the most frequently affected body parts, contributing to 58.2% of all cases of MSKd [15, 19–21]. Although these group-based exercise programs have been widely used, their clinical effectiveness needs to be evaluated in large samples or compared to usual individual physiotherapy care (UPC).

The primary objective of this pragmatic randomized controlled trial [22] is to evaluate the mid- and long-term effects of group-based supervised training programs on pain severity and functional limitations, in comparison with UPC in the treatment of military members presenting common MSKd. Secondary objectives include comparing both interventions 1) in terms of health-related quality of life, 2) pain-related fear, and 3) satisfaction with care received. We hypothesize that the group-based supervised training programs will be at least as effective as UPC to decrease functional limitations and pain severity, to improve health-related quality of life and pain-related fears and participants will be equally satisfied with both interventions.

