### Sample size

Based on our sample size calculation, calculated for our primary outcome (Pain Interference subscale of the Brief Pain Inventory) using data from a pilot study on military members with MSKd [33], 15 participants per diagnosis will be required per group for a total of 120 participants (60 participants/group) (G*Power 3.1.7; α = 0.05, 1-β = 0.95, Baseline mean: 2.9+/− 1.5 points, Follow-up mean: 0.8+/− 1.2 points, expected lost at follow-up = 15% [based on past experiences with this population]. This number will enable us to determine the effects of the interventions for each of the four conditions.

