### Outcomes

The primary outcome will be functional limitations, as measured with the Pain Interference subscale of the Brief Pain Inventory – Short Form (BPI). The secondary outcomes will include pain severity as measured with the Pain Severity subscale of the BPI, and health-related quality of life as measured with the EQ-5D-5L. As pain-related fear has been shown to influence outcomes in military members and conservative management reduces pain-related fears [20, 46], both interventions will also be compared on their impact on pain-related fears, measured with the Tampa Scale for Kinesiophobia (TSK) [38]. Furthermore, region-specific symptoms and functional limitations will be assessed using the Oswestry Disability Index (ODI) for low back pain, the shortened version of the Disabilities of the Arm, Shoulder and Hand (*Quick*DASH) for rotator cuff-related shoulder pain, Knee Outcome Survey Activities of Daily Living Scale (KOS-ADLS) for patellofemoral pain syndrome and Lower Extremity Functional Scale (LEFS) for lateral ankle sprain. To monitor compliance with home exercises, participants will be asked to maintain a weekly web-based logbook on RedCap during the 12 weeks of the intervention. Finally, participant’s satisfaction with treatment will be assessed at the end of the treatment (i.e., week-12) (see bellow for further description).

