### Statistical analyses

Descriptive statistics will be used for all outcome variables at each measurement time to summarise results. Baseline demographic data will be compared (independent *t*-tests and Chi-squared tests) to establish the comparability of groups. An intention-to-treat analysis will be used in which all participants will be analysed in the group to which they were assigned. In addition, sensitivity analyses will also be performed using per-protocol analyses; these analyses will allow to verify the consistency of the results in participants strongly compliant with the interventions (e.g., 75% attendance and home exercises). All dropouts and the reason for dropping out of the study will be reported. Any harm or unintended effects and co-interventions will be recorded. A 2-way ANOVA (2 Interventions [Group-Based or UPC] × 4 Times [0, 6, 12, 26 weeks]) will be used to analyse and compare the effects of the interventions on the primary outcome (Pain Interference Scale) and on four of the secondary outcomes (Pain intensity subscale, EQ-5D-5L, TSK) (SPSS, proc. GENLIN [Generalized Estimating Equations – GEEs]). Effect sizes (Cohen’s *d* for between-groups comparisons, Glass’s Δ for within-group comparisons) will be calculated. Nonparametric Analysis for Longitudinal Data (nparLD Package 2.1, R-software, v.3.6.1) will also be considered in cases where GEEs are not applicable (undefined distributions). If nparLD are used, effect sizes will be reported as relative treatment effect. Satisfaction with treatment will be compared between the two interventions using Chi-squared test for the PASS and Mann Whitney test or independent *t*-tests for satisfaction questions using the Likert scales. Exploratory analyses (using a similar statistical approach as for primary outcome) will be performed to compare the two interventions for each of the four conditions using the region-specific questionnaires (ODI, KOS-ADLS, *Quick*DASH, LEFS).

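### The primary objective covers two outcomes at two undefined horizons, the outcome section makes one of them secondary, and no visit or contrast is named to decide the primary result

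*Protocol article*

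**What the plan says.** **Objectives.** The abstract sets the primary objective as to "evaluate the mid- and long-term effects of these group-based training programs on pain severity and functional limitations", compared with usual individual physiotherapy care (UPC). The Background states the same objective in these words: "evaluate the mid- and long-term effects of group-based supervised training programs on pain severity and functional limitations, in comparison with UPC". Pain severity is missing from the secondary list: "Secondary objectives include comparing both interventions 1) in terms of health-related quality of life, 2) pain-related fear, and 3) satisfaction with care received".

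**Outcomes.** "The primary outcome will be functional limitations, as measured with the Pain Interference subscale of the Brief Pain Inventory". Then: "The secondary outcomes will include pain severity as measured with the Pain Severity subscale of the BPI". No time point is attached to the primary outcome.

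**Sample size.** The number was "calculated for our primary outcome (Pain Interference subscale of the Brief Pain Inventory"), using one follow-up mean whose week is not given.

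**Study design.** Evaluations are at baseline and weeks 6, 12 and 26. Week 6 is labelled as the middle of the intervention and week 12 as its end.

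**Statistical analyses.** The planned model is given as: "A 2-way ANOVA (2 Interventions [Group-Based or UPC] × 4 Times [0, 6, 12, 26 weeks]) will be used to analyse and compare the effects". It applies to Pain Interference as primary outcome and to secondary outcomes that include the BPI pain intensity subscale. The model is fitted by generalized estimating equations (GEE). Between-group effect sizes are promised, but no visit is given for them.

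**The concern.** Two things do not line up.

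First, pain severity belongs to the primary objective in the abstract and Background, yet it is a secondary outcome in Outcomes and Statistical analyses. A reader who starts from the objective expects it to count towards the main conclusion; a reader who starts from the outcome list does not. If interference came out similar between arms and pain severity worse, the two readers would report the primary objective differently.

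Second, the objective asks about two horizons, and the article neither defines them nor says which result answers the question. Mid-term could mean week 6 or week 12. A four-time, two-arm model yields a group term, a time term, an interaction and several visit-specific contrasts. Choosing among them after the results are known is the freedom that a primary outcome with a fixed time point should remove.

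**Working it through.** **1. Sections side by side**

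| Section | Pain Interference | Pain severity | Week |
|---|---|---|---|
| Abstract and Background, primary objective | primary (as functional limitations) | primary | mid- and long-term, undefined |
| Abstract and Background, secondary objectives | not listed | not listed | none |
| Sample size | primary | not mentioned | one unnamed follow-up |
| Outcomes | primary | secondary | none |
| Statistical analyses | primary | secondary | 0, 6, 12 and 26 together |

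The three operative sections agree on the outcome variable. The objective is the text out of line. The week and the contrast are fixed nowhere.

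**2. Does the sample size identify the primary contrast?**

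Inputs from Sample size: means 2.9 (SD 1.5) and 0.8 (SD 1.2), α = 0.05, power 0.95, loss 15%. The test is not stated; I assumed a two-sided two-sample t-test.

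- Difference: 2.9 − 0.8 = 2.1.
- Pooled SD: √((1.5² + 1.2²)/2) = 1.358. Standardised difference: 2.1/1.358 = 1.546.
- Noncentral t: n = 11 per group gives power 0.931 and n = 12 gives 0.951, so 12.
- Loss: 12/(1 − 0.15) = 14.1, rounded up to 15. Then 15 × 4 diagnoses × 2 groups = 120.

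The stated 15 and 120 reproduce as one comparison at one follow-up. That follow-up is unnamed, so the calculation does not say which visit decides, and it does not size a 2 × 4 interaction.

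**3. What would the interaction test show, if it decides?**

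Assumptions, not in the article: SD 1.2 at every visit (the follow-up SD), equal within-person correlation ρ = 0.5, and 51 completers per arm (60 × 0.85). With no arm difference at baseline, let c be the vector of arm differences at weeks 6, 12 and 26. The covariance of the estimated change-from-baseline contrasts is k(I + J), where k = 1.2² × (1 − ρ) × 2/51 = 0.02824, I is the 3 × 3 identity matrix and J the 3 × 3 matrix of ones. The noncentrality of the 3-df Wald test is [Σc² − (Σc)²/4]/k.

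| Differences at weeks 6, 12, 26 | Numerator | Noncentrality | Power (ρ = 0.5) | Power (ρ = 0.3 to 0.7) |
|---|---|---|---|---|
| 0.7, 0, 0 | 0.49 − 0.1225 = 0.3675 | 13.02 | 87% | 73% to 98% |
| 0.7, 0.7, 0.7 | 1.47 − 1.1025 = 0.3675 | 13.02 | 87% | 73% to 98% |
| 0, +0.5, −0.5 | 0.50 − 0 = 0.50 | 17.71 | 96% | 86% to 99.8% |

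A difference confined to week 6 and one sustained through week 26 give the test the same power. A pattern that favours opposite arms at weeks 12 and 26 gives more. A significant result therefore shows neither which horizon differs nor which arm does better.

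**4. Multiplicity, conditional only**

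Suppose each outcome at each horizon were tested at two-sided 0.05 and any one success counted. The chance of at least one false positive would be:

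- four tests: 1 − 0.95⁴ = 18.5% if independent; about 16% at an assumed correlation of 0.5 and 13% at 0.7, by multivariate-normal simulation;
- two outcomes at one time: 1 − 0.95² = 9.75% if independent; about 9% and 8% at the same correlations.

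A single pre-named test on Pain Interference holds 5%.

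**The case against.** The strongest reply is that the primary outcome is fixed: Sample size, Outcomes and Statistical analyses all name Pain Interference and nothing else. That stands. A reader might infer from the objective that the trial could declare success on either outcome at any visit; the three operative sections do not allow it.

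It can also be said that the article never states that a 3-df interaction is the planned test. That stands too. It gives a 2 × 4 model and names no deciding term, so the results in step 3 describe the natural reading of that model and not a stated plan.

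A reader might further infer that the plan carries a 13% to 16% false-positive rate. The document does not support that. It plans one longitudinal model on one primary outcome, and the correlations are assumed. The hypothesis also joins the two outcomes with *and*; if both had to succeed, testing each at 0.05 would not inflate the error.

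Finally, a condensed article may leave week definitions and contrasts to a fuller document. This carries some weight for model detail. It does not remove the disagreement between the objective and the outcome section, which are both current text, and the time point of the primary outcome is a protocol-level choice.

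**Conclusion.** The point holds in a limited form. The objective and the outcome section contradict each other on pain severity, and the horizons and the deciding contrast are not fixed. The outcome variable itself is consistent wherever the trial is sized and analysed.

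The consequence is that the analysis as described does not deliver the between-arm effect at the horizons that the objective names. If the interaction is the deciding term, its 87% and 96% power for patterns that do not answer the objective rest on the assumed SD, correlation and completer numbers; the direction of the argument does not. A non-significant interaction would not by itself support the hypothesis that group training does no worse than UPC; the absence of a margin for that claim is a separate matter and adds no weight here. The false-positive figures are conditional and should not be quoted as a property of this plan. The change should be made, but nothing here shows the sample size arithmetic to be wrong.

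**What to change.** 1. Reconcile the primary objective in the abstract and Background with Outcomes. Either keep functional limitations by BPI Pain Interference as the sole primary outcome and list pain severity under the secondary objectives, or declare both co-primary with a stated decision rule. The first matches the three sections that already agree.
2. Define mid-term and long-term in weeks.
3. Before unblinded results are seen, name one primary visit, week 12 or week 26. Take as the primary result the between-arm contrast at that visit, with its confidence interval, from the longitudinal model already planned. Make the other visits and the overall interaction secondary.

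The cost is wording in the objective, outcome and analysis text, and the other visits lose primary status. No new data, visits or participants are needed. The registry record could not be seen, so whether it needs a matching change should be checked.

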### Interventions

Before randomization, all participants will be evaluated by a PT (i.e., individual evaluation) [36, 37]. Then, participants will be randomized and will take part in their assigned 12-week intervention, which will consist of a maximum of 16 in-person sessions of 30 to 45 min each. An individualized home exercise program lasting 20–30 min, to be performed 3–4 times per week, will also be given to the participants in both groups.

If participants are symptom-free or do not have any functional limitations left before the end of the 16 sessions or 12 weeks, treatment will be ceased as judged by the PT supervising the group-based interventions or the individual treatment. The home exercises program will then be continued, with the possibility to resume the intervention if there is a recurrence of pain or functional limitations within the 12-week intervention period.

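### The hypothesis claims non-inferiority and equal satisfaction, but the plan has only tests of difference and sets no margin

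*Protocol article*

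**What the plan says.** The last paragraph of the Background section gives the hypothesis: "We hypothesize that the group-based supervised training programs will be at least as effective as UPC to decrease functional limitations and pain severity". The same sentence adds that "participants will be equally satisfied with both interventions". The primary objective just before it is worded neutrally, as an evaluation of mid- and long-term effects compared with usual individual physiotherapy care (UPC).

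Under Statistical analyses, a 2 (intervention) by 4 (time) ANOVA fitted through GEE "will be used to analyse and compare the effects of the interventions on the primary outcome (Pain Interference Scale"), with a nonparametric longitudinal method as fallback. Satisfaction is compared by chi-squared, Mann-Whitney or t-tests. Between-group Cohen's d, an intention-to-treat analysis and a per-protocol sensitivity analysis are also planned.

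The Sample size section uses "α = 0.05, 1-β = 0.95" with "Baseline mean: 2.9+/− 1.5 points" and "Follow-up mean: 0.8+/− 1.2 points" from a pilot study, and 15% loss to follow-up. It arrives at 15 per diagnosis per group, 120 in total.

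No section gives a non-inferiority or equivalence margin. Clinically important differences are quoted for the EQ-5D-5L, ODI, KOS-ADLS, QuickDASH and LEFS, but not for BPI Pain Interference, the primary outcome.

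**The concern.** A claim that one treatment is no worse than another needs a null hypothesis that it is worse by at least a stated amount, and data that reject that null. A claim of equality needs the same on both sides. Every test in the plan has the opposite null, that the arms do not differ. Rejecting it in favour of the group programme would show superiority, which covers non-inferiority. Short of that, the only test result that could look favourable to the hypothesis is a non-significant one. For equal satisfaction it is the only one in any case.

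Such a result becomes more likely as the trial gets smaller, noisier or less complete, so poor precision would work in favour of the hypothesis. The Discussion presents the group programmes as a way to manage more soldiers. A programme that is materially worse could then be taken up on evidence that does not exclude the deficit.

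This is not a detail left to an unseen analysis plan. The article itself states the hypothesis, the basis of the sample size and the primary test, and the three do not fit together.

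**Working it through.** **Step 1. What the stated sample size was built for.** Inputs from the Sample size section: means 2.9 and 0.8, SDs 1.5 and 1.2, alpha 0.05, power 0.95, loss 15%.

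- Difference: 2.9 − 0.8 = 2.1 points.
- Pooled SD: √((1.5² + 1.2²)/2) = 1.358, so d = 2.1/1.358 = 1.546.
- Two independent means, two-sided 0.05, noncentral t: 12 per cell gives power 0.951 (11 gives 0.931).
- Dropout: 12/0.85 = 14.1, rounded up to 15. Then 15 × 4 diagnoses × 2 arms = 120.

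The stated figure is reproduced as a test of difference on 2.1 points. Sidedness is not stated, and one other reading also gives 15 (one-sided, SD 1.5), but every reading rests on the same 2.1 points. That is a change from baseline to follow-up. It is neither a between-arm difference nor a usable margin, since a margin of 2.1 would allow the whole expected improvement to be lost.

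**Step 2. How often a real deficit would go undetected.** Assumptions: a t-test at one time point, two-sided 0.05; 60 × 0.85 = 51 per arm overall and 15 × 0.85 = 12.75 per arm within a diagnosis; a true deficit of 0.5 points, chosen for illustration (0.5/2.1 = 24% of the expected gain).

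SE = SD × √(2/n); noncentrality = 0.5/SE; P(non-significant) = P(|T| < critical t), with T noncentral t on 2n − 2 degrees of freedom. The critical values are 1.984 (n = 51) and 2.066 (n = 12.75).

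| SD | SE, n = 51 | Noncentrality | Non-significant, overall | Non-significant, one diagnosis |
|---|---|---|---|---|
| 1.2 | 0.238 | 2.10 | 45% | 83% |
| 1.358 | 0.269 | 1.86 | 55% | 86% |
| 1.5 | 0.297 | 1.68 | 62% | 87% |

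**Step 3. What the planned size gives for a proper non-inferiority test.** The documents give no margin, so those below are assumptions. One-sided 0.025, true difference 0; power = P(T > critical t) with noncentrality margin/SE.

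| Margin (points) | Power, 51 per arm, SD 1.5 to 1.2 | Power, 12.75 per arm, SD 1.5 to 1.2 |
|---|---|---|
| 0.5 | 38% to 55% | 12% to 17% |
| 0.75 | 71% to 88% | 23% to 33% |
| 1.0 | 92% to 99% | 36% to 52% |

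A normal approximation moves the overall figures by about one percentage point at most.

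**Step 4. Satisfaction.** The half-width of the 95% CI for a difference in the proportion answering yes on the PASS is 1.96 × √(2p(1 − p)/51). The documents give no rates. For assumed p of 0.9, 0.8 and 0.7 it is 0.116, 0.155 and 0.178, that is about 12 to 18 percentage points. An interval of that width cannot establish equality without a stated tolerance.

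**The case against.** The strongest reply is that the trial is never called a non-inferiority or equivalence trial. The objective is comparative, a group-by-time model addresses it, and the hypothesis may only express what the investigators expect. This stands in part: it would be too strong to say that the trial cannot answer its own question, and rewording one sentence would remove the mismatch. But the sentence is put forward as the hypothesis, and nothing planned can test it short of superiority.

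A reader might infer that the investigators intend to treat p > 0.05 as proof that the programmes are no worse. The article does not say so. It states no rule for a non-significant result, and it plans Cohen's d alongside the tests. The point is about what the plan could support, not about a declared intention. An effect size without a margin does not fill the gap.

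A reader might also see a conflict between the per-protocol set, "participants strongly compliant with the interventions (e.g., 75% attendance and home exercises"), and the Interventions section, where for participants who have recovered "treatment will be ceased as judged by the PT supervising the group-based interventions or the individual treatment". That follows only if attendance is counted against all 16 sessions. Sixteen is a maximum, no denominator is given, and counting sessions up to discharge fits both sections. The denominator can reasonably be left to the full protocol or analysis plan.

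Finally, the figures are for a single time point. Repeated measures or baseline adjustment could improve precision, but the article gives no correlation from which to calculate by how much.

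**Conclusion.** The mismatch is real and is visible in the article itself: parity hypotheses, tests of difference only, a sample size based on change from baseline, and no margin. A non-significant result would be weak evidence. A true 0.5-point deficit would be missed about 45% to 62% of the time overall and 83% to 87% of the time within a diagnosis, assuming one time point, 15% loss and SDs of 1.2 to 1.5.

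Whether 120 participants are enough for non-inferiority depends on a margin that only the investigators can justify. At true equality the size is weak for 0.5 points, moderate to good for 0.75 and strong for 1.0, although at 0.75 it stays below the 95% power that the article plans for. Within a diagnosis it is inadequate at all three margins, despite the stated aim of determining effects in each condition.

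**What to change.** Before unblinding:

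1. Name one primary time point and a margin on BPI Pain Interference that is justified clinically, not read back from what the sample size can deliver.
2. Conclude non-inferiority only if the upper limit of the two-sided 95% CI for (group − UPC) at that time point, from the planned model, lies below the margin. Keep intention-to-treat as the main analysis and use the per-protocol analysis already planned as a consistency check.
3. State the power that the planned size gives for that margin, with the SD assumed.
4. Report results by condition as estimates with confidence intervals, without a non-inferiority conclusion.
5. For satisfaction, report the between-arm difference with its 95% CI, and do not conclude equality from p > 0.05.

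If no margin can be justified, reword the hypothesis as a question of difference and draw no conclusion of parity.

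The cost is some wording and one clinical decision. No new data are needed unless the margin chosen is too tight for 120 participants, in which case the sample size has to be revisited or the limited power acknowledged.
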